### Statistical analysis

The data will be entered and analyzed with SPSS 14.0, and the following statistical procedure will be undertaken:

1. Descriptive analysis of defined variables.

2. Mean comparison tests for quantitative variables and comparison of proportions for qualitative data, among independent variables to check the comparability of the groups.

3. Mean comparison tests for each outcome variable according to the treatment group (differences pre-post treatment in both treatment groups as well as differences between them)

4. Multivariate analysis to determine the influence of independent variables in the evolution of each outcome variable.

A descriptive analysis of drop outs will also be made in order to determine if there are correlating patterns.

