**Figure 1 F1:**
[figure not shown]
**Randomised controlled trial design**.

The patients will be classified into five levels according to the Gross Motor Function Classification System (GMFCS) and subsequently randomly divided into two treatment groups.

1.- Treatment Group with hippotherapy simulator switched on.

2.- Treatment Group with hippotherapy simulator switched off (without rhythmic movement).

The randomising will be centralised and generated by computer according to stratified groups to ensure a similar distribution of the possible confounding variables in both groups. The assignation sequence will be concealed.

Ten treatment sessions (one weekly) will be given in each modality, in which the children will do different activities proposed by the physiotherapist according to their motor possibilities.

In the treatment sessions with the hippotherapy simulator switched on, the children will maintain the sitting position for 15 minutes on the simulator, with an active extension of the trunk, stabilization of the pelvis and abduction of hips while the simulator produces a rhythmic and repetitive movement that is similar to a walking horse. In the treatment sessions with the simulator switched off (without providing the rhythmic movement), the children will maintain the active extension of the trunk, stabilization of the pelvis and abduction of hips but they won't benefit from the rhythmic effects produced by the hippotherapy simulator. That is, the children who sit on the simulator that is switched off will receive the same treatment except that they won't receive rhythmic movement from the simulator (it would be similar to sitting on a barrel or another device in which they maintain this sitting position, similar to other studies published^7^).

Children not included in the group with the simulator switched on will be offered the possibility to receive ten more treatments with the simulator switched on once the research has concluded.

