### Study variables

The hippotherapy simulator used for this study is "Core Trainer Exercise Equipment, JOBA" produced by Matshuita (Panasonic), and allows working at 9 speeds and 3 predefined programmes (basic conditioning, waist, hips).

This simulator was designed to be used in fitness centres. To make it easier to use the system offers three automated training routines:

WORKOUT (Side-To-Side)

WAIST (Forward Tilt)

HIPS (Backward Tilt)

These training routines can automatically modify the speed and tilt of each one of the training sub phases

When planning a work session with the JOBA commercial Simulator, the time, tilt and speed adjustment allows for unequivocally defining the test parameters. Therefore using the same Simulator and knowing these parameters, the repeatability of the test is totally guaranteed. In the case of our study, we have listed the exact programme that was used, which is Side-To-Side WORKOUT.

The study variables will be measured with the instruments showed in table 1 (see table 1).

**Table 1 T1:** Study variables and instruments for measurement.

STUDY VARIABLES	INSTRUMENTS
Sitting balance	SAS (Sitting Assessment Scale) [21]

Muscular activity in hip adductors	Surface Electromyography (EMG)

Hip abduction range of motion	Electronic inclinometer and traditional goniometer

Gross motor function	Gross Motor Function Measure (GMFM)

There are four outcome variables:

- Sitting balance

- Measurement of hip abduction range of motion

- Electromyographic activity in adductors

- Global motor development

The outcome variables will be measured at three different times during the research. A first measurement will be made at the beginning of the study, a second one when the ten treatment sessions have concluded, and a third measurement after the 3-month follow-up period. Moreover, two of these outcome variables (hip abduction range of motion and Electromyographic activity in adductors) will also be measured before and after each treatment session.

Control of confounding variables (independent variables) will be carried out on each and everyone of the outcome variables studied. The confounding variables considered to be studied will be those listed below:

- Sociodemographic variables: sex, age and physical activity.

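### The stated treatment comparison leaves out the GMFCS level used to stratify randomisation and uses baseline only through change scores, which may cost precision without biasing the estimate

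*Protocol article*

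**What the plan says.** All places are in the protocol article.

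- **Randomisation** (Study design, text under Figure 1): "The patients will be classified into five levels according to the Gross Motor Function Classification System (GMFCS) and subsequently randomly divided into two treatment groups". The same section adds: "The randomising will be centralised and generated by computer according to stratified groups". GMFCS is the only classification named there.
- **Baseline** (Study variables): "A first measurement will be made at the beginning of the study". This covers all four outcomes. They are measured again after the ten sessions and after the 3-month follow-up.
- **Treatment comparison** (Statistical analysis, item 3): "Mean comparison tests for each outcome variable according to the treatment group", explained in brackets as "differences pre-post treatment in both treatment groups as well as differences between them". No stratum or covariate is named.
- **Multivariable step** (Statistical analysis, item 4): "Multivariate analysis to determine the influence of independent variables in the evolution of each outcome variable".
- **Covariate list** (Study variables): "Sociodemographic variables: sex, age and physical activity", followed by clinical items such as drug treatment, diagnosis, previous riding therapy, surgery, botulinum toxin and orthoses. Neither GMFCS nor the baseline value of the outcome appears.

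**The concern.** Stratifying by severity makes the groups alike in severity. A test that ignores the strata still counts between-stratum variation as noise, so its standard error is larger than the design warrants. This applies only to variation in the quantity tested, which here is the pre-post change.

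A second inefficiency is separate. Subtracting the baseline forces its coefficient to be 1, whereas regression adjustment estimates it and never does worse in large samples.

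With 37 children, deliberately not limited to milder cases, precision is scarce. At stake are the width of the intervals and the chance of missing a real effect. Bias is not at stake.

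**Working it through.** **The plan's own figure.** The sample size uses 60% against 10% improving, with power 0.90. Alpha is not stated; two-sided 0.05 is assumed.

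n = [1.960·√(2·0.35·0.65) + 1.282·√(0.6·0.4 + 0.1·0.9)]² / 0.5² = (1.322 + 0.736)² / 0.25 ≈ 16.9, so 17 per group, as stated. This is for a binary outcome, so it does not fix the power of the mean comparisons.

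**Baseline alone.** Let ρ be the correlation of baseline and post-treatment values, with equal variances of 1. The change score has variance 2(1−ρ) and analysis of covariance (ANCOVA) has residual variance 1−ρ². The ratio is (1+ρ)/2. At 17 per group:

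| ρ | variance ratio | CI width ratio | power 0.80 becomes |
|---|---|---|---|
| 0.5 | 0.75 | 0.87 | 0.90 |
| 0.7 | 0.85 | 0.92 | 0.86 |
| 0.8 | 0.90 | 0.95 | 0.84 |
| 0.9 | 0.95 | 0.97 | 0.82 |

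**Baseline and GMFCS together.** These gains overlap and must not be added, so they were simulated jointly. All inputs below are assumed except the total of 37 and the five levels:

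- strata of 7, 7, 7, 8 and 8, balanced allocation within strata, 4,000 runs per scenario;
- ρ: within-stratum correlation;
- B: share of baseline variance explained by GMFCS;
- γ: dependence of change on GMFCS, in SD per SD of level.

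The change score has variance 2(1−ρ)(1−B) + γ². ANCOVA with baseline and stratum has (1−ρ²)(1−B). The table compares the t-test on change with ANCOVA on baseline plus four GMFCS indicators.

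| | ρ | B | γ | effect (SD) | CI half-width | fall | power |
|---|---|---|---|---|---|---|---|
| A | 0.5 | 0.5 | 0 | 0.66 | 0.469 → 0.417 | 11% | 0.788 → 0.863 |
| B | 0.5 | 0.7 | 0 | 0.50 | 0.363 → 0.323 | 11% | 0.762 → 0.855 |
| C | 0.8 | 0.5 | 0 | 0.43 | 0.297 → 0.289 | 3% | 0.807 → 0.831 |
| D | 0.8 | 0.5 | 0.2 | 0.43 | 0.326 → 0.287 | 12% | 0.767 → 0.842 |
| E | 0.9 | 0.7 | 0 | 0.24 | 0.162 → 0.162 | 0% | 0.824 → 0.823 |
| F | 0.9 | 0.7 | 0.2 | 0.24 | 0.213 → 0.163 | 23% | 0.621 → 0.814 |

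Check on F: variances 2·0.1·0.3 + 0.04 = 0.100 and 0.19·0.3 = 0.057; √0.57 = 0.755, a fall of about 24%, which agrees. A second set of change-score scenarios, also with correlations of 0.5 to 0.9, gave falls of 0% to about 18%, and power moving from 0.66–0.80 to 0.80–0.88.

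**Type I error** (effect 0, ρ = 0.8, B = 0.5). With γ = 0 it is 0.046 on change scores and 0.047 adjusted. With γ = 0.3 it is 0.021 and 0.046, and the half-width falls from 0.360 to 0.289 (20%).

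**If the groups are compared on post-treatment values only** (ρ = 0.8, B = 0.5, γ = 0), the half-width is 0.67 against 0.29 and the type I error is 0.006.

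**The case against.** **Baseline is used.** A reader who stops before the bracket in item 3 might infer that baseline is ignored. The bracket says pre-post differences are compared. This objection stands. What remains is an efficiency argument, worth only 5% of variance at ρ = 0.9.

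**Severity may cancel.** If GMFCS shifts baseline and post-treatment values equally, it drops out of the change score, however strongly it predicts the raw scores. This also stands, and scenario E shows a gain of nothing. It limits a stronger reading. With 36 children in near-equal strata and an effect of 0.8 SD, the unadjusted test has type I error 0.3% and power 0.68 against 0.95 adjusted if GMFCS explains 60% of the variance of the tested quantity. For this trial that quantity is change. The share is γ²/[γ² + 2(1−ρ)(1−B)]: 17% in D and 40% in F. Reaching 60% needs, for example, γ = 0.3 with ρ = 0.9 and B = 0.7 (0.09/0.15). Nothing in the article supports choosing that combination.

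**Adjustment is planned.** The article promises confounder control for every outcome, and item 4 is multivariable. But item 4 is framed as a study of what the listed variables do. It is not named as the treatment estimate, and its list lacks GMFCS and baseline.

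**This is detail for the full plan.** The article names no specific test and is condensed, and the list might not be exhaustive. Even so, it states both a type of comparison and an explicit list, and the objection is to those.

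**No false positives follow.** True: under randomisation the change-score comparison is unbiased, and ignoring the strata errs on the conservative side. That makes this a matter of precision and not of validity.

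**Conclusion.** The point holds as a loss of efficiency of uncertain size. The stratification factor enters no stated analysis, and baseline enters only through change scores.

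In the scenarios run, adjustment narrows the interval by 0% to roughly 20% (23% in the most favourable one). It raises power by between nothing and 0.15 to 0.19. The unadjusted type I error was 0.046 and 0.021 in the two null scenarios. These ranges describe those scenarios and are not bounds: where GMFCS explains 40% of the tested variance, the simulation with 36 children gave 0.013.

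Everything rests on assumed correlations, GMFCS effects and near-equal strata, because the article gives none of these. It also rests on reading the strata as the GMFCS levels, which is natural but not said outright. The loss is much larger if the between-group difference means post-treatment values only. A reader might infer that power is certainly lost or that the treatment estimate is biased; the article supports neither.

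**What to change.** - For each outcome, make the between-group treatment estimate an analysis of covariance of the post-treatment value on treatment group, the baseline value of that outcome and GMFCS. Report the adjusted difference with its 95% CI.
- Enter GMFCS as a linear score or in merged levels, given 37 children. Do not put the whole confounder list into this model, as it has too many terms for the sample.
- Add GMFCS to the covariate list, and say outright that the randomisation strata are the GMFCS levels, if they are.

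**Cost.** A change of wording and no new data. The model uses two degrees of freedom (baseline plus linear GMFCS) or up to five (baseline plus four indicators). Where GMFCS adds nothing, the four indicators cost about 0.003 to 0.004 in power: at ρ = 0.5, 0.898 becomes 0.895.

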### Objectives

The main objective to be achieved in this project is to study the therapeutic relevance of a hippotherapy simulator for the treatment of children with cerebral palsy (considering four outcome variables, which are: sitting stability, muscle activity in hip adductors, range of hip abduction mobility and global motor development). We will study and divide the effect of the hippotherapy simulator into two aspects:

- Maintenance of a therapeutic stance.

- Rhythmic and repetitive movement produced by the simulator, that is similar to the normal mechanics of the human step.

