### Sample

The subjects of the study are children between 4 and 18 years old with CP, who attend schools run by the Education Department of the Government of Aragon (Spain) and whose tutors have signed an informed consent form.

Regarding the sample size, a calculation of statistical power was made previous to the study. The calculation of statistical power was based on a non-published introductory research of the effects of a commercialized hippotherapy simulator for cerebral palsy children. In this study, an improvement of 60% was obtained in cases against 10% of improvement in controls, so improvement probability is considered to be at least double in cases than in controls (odd ratio of 2). In order to assure a power of 0.90 the sample should be 17 in every group (total sample 34). The sample size was considered to be 10% greater due to possible drop-outs (37-38 children).

All CP children that fit the inclusion criteria were selected to participate (37 children). In this study it is hoped to assign at least 18 subjects randomly to each experimental condition.

In cases where tutors or children do not wish to participate, the following variables will be recorded: Sex, age, level of Gross Motor Function Classification System and cause to refuse to participate.

The exclusion criteria are as follows:

- Children who have undergone selective dorsal rhizotomy

- Acute convulsions not controlled by medication

- Allergy to electrode adhesives

- Visual impairment not corrected with glasses

- Those circumstances or associated illnesses that in the judgment of the researcher might interfere with the results or be detrimental to the children.

- Inability to attend intervention sessions or refusal to participate.

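### Four co-equal outcomes carry the main objective and no primary outcome or time point is named, so the chance of a false-positive finding exceeds the nominal level

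*Protocol article*

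**What the plan says.** The Objectives section of the protocol article states one main objective, the therapeutic relevance of the simulator, and defines it by "considering four outcome variables, which are: sitting stability, muscle activity in hip adductors, range of hip abduction mobility and global motor development". The Study variables section repeats the list under "There are four outcome variables" and ranks none of them.

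On timing, Study variables says "The outcome variables will be measured at three different times during the research": at baseline, after the ten sessions, and after a 3-month follow-up. Hip abduction range and adductor EMG "will also be measured before and after each treatment session". The description of the design gives the number of sessions: "Ten treatment sessions (one weekly) will be given in each modality".

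The Statistical analysis section, item 3, prescribes "Mean comparison tests for each outcome variable according to the treatment group" and explains these as "differences pre-post treatment in both treatment groups as well as differences between them". It does not say which post-baseline time the comparison uses.

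The Sample section reports that "a calculation of statistical power was made previous to the study". That calculation uses 60% improvement against 10%, power 0.90 and 17 children per group. It does not say on which of the four outcomes improvement is judged, and it gives no significance level.

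**The concern.** The trial asks one question, whether the rhythmic movement is therapeutically relevant, and plans at least four separate between-group answers to it. The article does not say which answer decides. A reader of the eventual report could not tell whether the outcome given most emphasis was chosen before or after the data were seen.

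Two things are at stake. If there is no true effect, the chance that some outcome reaches significance is well above the level of any single test. In addition, the power statement belongs to no identifiable outcome, so a null result on any one of them cannot be read against the claimed 0.90.

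**Working it through.** **Inputs from the protocol article.** Four outcomes (Objectives; Study variables). Two post-baseline assessments of each, at the end of treatment and at 3 months (Study variables). Improvement 60% against 10%, power 0.90, 17 per group (Sample).

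**Assumptions, because the article gives no figure.** Two-sided 0.05 per test. Correlation between test statistics from 0 to 0.9, with 0 and 0.5 as the main range.

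**Step 1: reproduce the stated sample size.** The pooled two-proportion formula without continuity correction, with p̄ = (0.60 + 0.10)/2 = 0.35, is

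n = [z(1−α/2)·√(2·p̄·(1−p̄)) + z(0.90)·√(p1(1−p1) + p2(1−p2))]² / (p1−p2)²

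With α = 0.05: [1.960·√0.455 + 1.282·√0.33]² / 0.25 = 16.9, so 17 per group. Power at 17 per group is 0.901. The stated figure is reproduced, so two-sided 0.05 is a reasonable assumption. It is not proof: a one-sided version with continuity correction gives 18, which is close.

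**Step 2: chance of at least one false-positive between-group result, no true effect.** For m independent tests this is 1 − 0.95^m:

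- m = 4 (end of treatment only): 1 − 0.95⁴ = 0.185
- m = 8 (end of treatment and 3 months): 1 − 0.95⁸ = 0.337

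For correlated tests, using equally correlated normal statistics:

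| Correlation | 4 tests | 8 tests |
|---|---|---|
| 0 | 18.5% | 34% |
| 0.3 | 17% | 30% |
| 0.5 | 16% | 25% |
| 0.7 | 13% | 19% |
| 0.9 | 9% | 12% |

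Every entry exceeds 5%.

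**Step 3: only false positives that favour the moving simulator.** Counting z > 1.96 alone, each test has a 2.5% chance. Four tests give 1 − 0.975⁴ = 9.6% if independent and 7.8% at correlation 0.5. Eight give 1 − 0.975⁸ = 18% and 12.5%.

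**Step 4: cost of adjusting over four comparisons.** The strictest Holm step tests at 0.05/4 = 0.0125, with z = 2.498. On the 60% against 10% basis, power at 17 per group is Φ[(0.5·√17 − 2.498·√0.455)/√0.33] = Φ[(2.062 − 1.685)/0.574] = 0.744. The formula in Step 1 then gives 23.4, so 24 per group would be needed for 0.90.

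**The case against.** **Multiplicity methods may be specified elsewhere.** This is a journal article, and adjustment procedures and success rules are often left to the full protocol or an analysis plan, neither of which is shown. That stands, and silence on adjustment is not itself the finding. It does not cover the choice of primary outcome and time point, which belongs in the protocol. Nor is the article merely silent here: it sets out the objective, the outcome list and the tests, and treats the four outcomes as equals throughout.

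**The session-level data.** A reader might infer that two outcomes are tested at all ten sessions. That would add 2 × 10 = 20 comparisons to the eight and raise the error to 1 − 0.95²⁸ = 76% if independent, so that a false positive looks likely. The article does not support this. It says those outcomes are measured around each session, and the analysis section plans no session-by-session test. Even with 28 tests, the figure is 49% at correlation 0.5 and 33% at 0.7. On the readings that the text supports, the error is at most about 34%.

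**Any single significant result counts as success.** A reader might infer this too. The article states no decision rule of any kind, so the fair statement is that the rule is open.

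**Direction.** The two-sided figures include results favouring the switched-off arm. For a false claim of benefit, the four-test figure is about 8% to 10%, against 2.5% for one test. This objection is right as to size. The inflation remains, and the Abstract also aims to detect contraindications, so errors in both directions matter.

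**Conclusion.** The point holds in a limited form. The main objective depends on four unranked outcomes, each with its own mean comparison tests, and the article fixes neither a primary outcome nor a primary time point. The sample-size calculation does not fill the gap.

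The chance of at least one false-positive between-group result is about 16% to 19% for the four end-of-treatment comparisons, and about 25% to 34% if the 3-month comparisons are also tested. These ranges assume two-sided 0.05 per test, correlation between 0.5 and 0, and no true effect. Stronger correlation lowers them, but they stay above 5% up to the 0.9 explored. The within-arm pre-post tests are not counted, because they do not test the treatment difference.

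The trial remains feasible. What it lacks is a prespecified test for its main claim.

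**What to change.** **Preferred.** Before unblinding, name one of the four outcomes, at the end of the ten sessions, as the primary between-group comparison. Choose it on clinical grounds: order of listing is no guide, since the Abstract puts motor development first and Study variables puts sitting balance first. State how improvement in the sample-size calculation is defined on that outcome. The level stays at 0.05 and, on the 60% against 10% basis, 17 per group still gives 0.90. The cost is wording, plus the work of linking the calculation to the outcome.

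**Alternative.** Keep the four end-of-treatment between-group comparisons as the confirmatory family and test them with Holm's procedure at an overall two-sided 5%. The power must then be restated: at 17 per group it falls from 0.90 to about 0.74 at the strictest step, and 24 per group (48 in total) would be needed to restore it. The Sample section says that all 37 eligible children were selected, so there may be no room to enlarge the trial.

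**In either case.** State the significance level. Label the 3-month, session-level and within-arm comparisons secondary or exploratory. Base the conclusion on therapeutic relevance on the confirmatory result only.

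### The only stated between-arm outcome test is an unadjusted pre-post comparison, which leaves the scheduled 3-month visit without a between-group comparison and uses neither the baseline value nor the GMFCS strata

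*Protocol article*

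**What the plan says.** **Schedule.** In the Study variables section, "The outcome variables will be measured at three different times during the research": at the start, when the ten sessions are finished, and "a third measurement after the 3-month follow-up period". This applies to all four outcomes: sitting balance, hip abduction range, adductor EMG and gross motor function. Hip range and EMG "will also be measured before and after each treatment session", and the Study design section says "Ten treatment sessions (one weekly) will be given in each modality".

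**Allocation.** The Study design section classifies children into five GMFCS levels and then divides them at random. The computer randomisation is described as stratified.

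**Analysis.** The Statistical analysis section lists four steps. Steps 1 and 2 are descriptive statistics and a check of group comparability. Step 3 is mean comparison tests for each outcome by treatment group, specified as "differences pre-post treatment in both treatment groups as well as differences between them". Step 4 is "Multivariate analysis to determine the influence of independent variables in the evolution of each outcome variable".

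**The concern.** Step 3 goes beyond a general label: it names both a type of test and a contrast. Taken at its word, that contrast uses two of the three scheduled visits. If it is followed, the trial brings every child back at 3 months and then has no stated test of whether the arms differ at that visit. If it is not followed, the 3-month contrast has to be chosen later, possibly with the data in view.

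The same step compares raw changes. In a small trial across all five GMFCS levels, starting values will vary widely, and a comparison of raw changes uses less of the baseline information than a baseline-adjusted comparison does. It also ignores the factor on which randomisation was stratified.

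**Working it through.** The plan gives no figure on this point. Its one calculation, the sample size, is reproduced first to show that it neither depends on the visits nor settles the matter.

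1. **Sample size.** The Sample section says that "an improvement of 60% was obtained in cases against 10% of improvement in controls", and asks for power 0.90 with 17 per group. Two-sided alpha of 0.05 is assumed, since none is stated. With mean proportion 0.35:
   - n = [1.960·√(2·0.35·0.65) + 1.282·√(0.6·0.4 + 0.1·0.9)]² / (0.6 − 0.1)²
   - n = (1.322 + 0.736)² / 0.25 ≈ 16.9, so 17 per group, with power 0.901
   - 34 × 1.1 = 37.4, which matches 37-38 children

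   The figure reproduces. It rests on a proportion improved and says nothing about which visit is compared.

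2. **Visits scheduled against visits compared.** Four outcomes at two post-baseline visits give 4 × 2 = 8 possible between-arm contrasts. Step 3, read literally, covers the four after ten sessions. The four at 3 months are not named.

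3. **Does step 4 supply them?** It concerns the influence of independent variables. The Study variables section uses that term for the confounders and lists them: sex, age, physical activity, medication, diagnosis, hippotherapy history, off-trial hippotherapy, surgery, botulinum toxin and orthoses. Treatment group, baseline outcome value and GMFCS level are not named in that list, and no visit is named in step 4. The word evolution could include 3 months, but nothing says that it does.

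4. **What baseline adjustment is worth.** Assume equal variance σ² at both visits and a correlation r between them. A change score has variance 2(1 − r)σ². The ANCOVA residual has variance (1 − r²)σ². Their ratio, ANCOVA to change score, is (1 + r)/2. The article gives no r, so as an assumed range:

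| r | ratio |
|---|---|
| 0.3 | 0.65 |
| 0.5 | 0.75 |
| 0.7 | 0.85 |

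   As r approaches 1 the ratio approaches 1 and the gain disappears.

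5. **What adjustment costs.** A two-group t-test in 37 children leaves 37 − 2 = 35 degrees of freedom. An ANCOVA with intercept, treatment, baseline value and four GMFCS terms leaves 37 − 7 = 30. The two-sided 5% critical value moves from about 2.03 to 2.04. Five levels in 37 children average 37/5 = 7.4 per level, so some may be sparse.

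6. **Per-session data.** Ten sessions × 2 = 20 values per child for each of hip range and EMG. No step in the Statistical analysis section mentions them.

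**The case against.** The strongest reply is that this is a condensed article. A four-line outline commonly leaves the handling of each time point to a full protocol or SAP, and silence alone is not an error. Step 3 also applies to each outcome variable. Both later visits fall after treatment, so a generous reader could take post to include the 3-month visit. The Objectives section sets no separate aim on persistence of effect. An unadjusted comparison of changes is a legitimate analysis of a randomised trial, and a mixed model is one acceptable choice among several.

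Much of this stands. The 3-month visit is not expressly excluded, and the unadjusted test is less efficient rather than invalid. What remains is that the article does state its contrast, and the stated contrast does not match its own schedule and stratification. A fuller plan that followed step 3 would carry the gap forward.

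Two stronger readings are tempting and not supported:

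- **That pre-post comparison is the plan's only method.** Step 4 exists, so it is only the sole stated comparison between arms.
- **That repeated session values will be tested as if independent.** No section says so. One change score per child breaks no independence assumption, and child-level mean session changes could be compared with the same kind of test. If the ten session changes per child were pooled, the design effect would be 1 + 9ρ, where ρ is the within-child correlation of those changes. Assumed ρ of 0.1, 0.3, 0.5 and 0.7 gives 1.9, 3.7, 5.5 and 7.3. The true error at a nominal 5%, 2[1 − Φ(1.96/√design effect)], would be about 15%, 31%, 40% and 47%. These figures describe an analysis that the plan does not propose, at correlations that it does not give. They are not a property of this plan.

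**Conclusion.** The point holds in limited form. The one stated between-arm comparison, read literally, omits half of the post-baseline contrasts that the schedule makes available, and it uses neither baseline adjustment nor the GMFCS strata. Step 4 does not clearly repair either omission. The precision at stake depends on the unknown baseline-to-follow-up correlation and may be small where that is high. The conclusion rests on two readings: that pre-post means baseline to the end of the ten sessions, and that the GMFCS levels are the randomisation strata. Both are the natural ones. This is a change worth making before analysis. It does not show that the planned test would give biased or falsely significant results.

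**What to change.** For each outcome, replace the between-group test in step 3 with a linear mixed model over the two post-baseline visits. Include treatment, visit, treatment-by-visit, baseline value, GMFCS level (sparse levels combined by a rule set in advance) and a random child effect. An ANCOVA at each visit with the same covariates is an acceptable alternative. Report the between-group difference after ten sessions and at 3 months. The mixed model also keeps a child who has only one of the two later visits, which is useful given the 10% drop-out allowance.

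As a precaution only: if the per-session hip range and EMG values are compared between arms, reduce each child to one mean session change, or use a random child effect.

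The cost is a few lines of wording, slightly more analysis work and the few degrees of freedom shown above. No new data are needed.
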